### Outcomes

The primary outcome of the study is the proportion of patients with a clear resection margin. A resection margin is considered clear (R0), if there are no tumour cells in any of the resection surfaces as determined by microscopy (resection margin more than 0 mm).

Secondary outcomes are:

3- and 5-year local re-recurrence-free survival, defined as the interval between surgery and local re-recurrence;3- and 5-year progression-free survival, defined as the interval between randomization and progression of local recurrence, local re-recurrence, distant metastases or death;3- and 5-year metastasis-free survival, defined as the interval between randomization and development of distant metastases;3- and 5-year disease-free survival, defined as the interval between surgery and local re-recurrence, distant metastases or death;3- and 5-year overall survival, defined as the interval between randomization and death;pathological response, graded according to the Mandard grading system^40^;radiological response, scored according to the magnetic resonance tumour regression grade (mrTRG);compliance rate with induction chemotherapy (i.e., the number of patients receiving CAPOX, FOLFOX or FOLFIRI as initial regimen will be tabulated, and dose modification and reason will be summarized for each regimen);toxicity of induction chemotherapy, scored from day 1 of the first cycle of induction chemotherapy until 1 month after the final administration, and graded according to the Common Terminology Criteria for Adverse Events (CTCAE) version 5.0;compliance rate with chemoradiotherapy, calculated as the total radiotherapy dose received divided by the total planned dose;toxicity of chemoradiotherapy, scored from start of radiotherapy until 3 months after the final dose of radiotherapy, and graded according to CTCAE version 5.0;number of patients undergoing surgery;surgical characteristics (e.g., type of resection, ostomy, use of intraoperative radiotherapy, blood loss, duration of operation, intraoperative complications);major surgical morbidity rate scored from the date of surgery to 3 months after surgery, and graded according to the Clavien–Dindo classification^41^;quality of life, assessed with EQ-5D-5L™, QLQ-C30 and QLQ-CR29 questionnaires at inclusion, and at 3 and 12 months after surgery; andcost-effectiveness and cost–utility, based on Dutch costing guidelines for healthcare, the case report forms, and the EQ-5D-5L™ questionnaire.

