### Statistical methods

Demographics, patient, and tumour characteristics will be presented for each treatment arm. Continuous data will be reported as mean (standard deviation) or median (interquartile range or 95 per cent confidence interval), depending on the distribution. Categorical data will be reported as count with percentage. All statistical tests will be two-sided and *P* < 0.050 will be classified as statistically significant. Patients initially randomized but considered ineligible afterwards, based on information that should have been available before randomization, will be excluded from all analyses.

Analysis of the primary endpoint of this study, the proportion of patients with an R0 resection, will be based on the intention-to-treat principle using Fisher’s exact test. In addition, a per-protocol analysis will be performed as a sensitivity analysis.

All survival curves will be constructed according to the Kaplan–Meier method, and the log rank test will be used to compare treatment arms, adjusting for stratification factors at randomisation (previous radiotherapy, previous systemic therapy, and expert centre). In addition, hazard ratios will be calculated using a Cox proportional hazards regression model, adjusting for stratification factors. Metastasis-free survival, progression-free survival, and overall survival will be based on the intention-to-treat group. Local re-recurrence free survival and disease-free survival analyses will include only patients who underwent surgery.

Data on surgical characteristics, histopathological characteristics, and major surgical morbidity will be presented by treatment arm, and will be derived only for patients who underwent surgery. The number of patients undergoing surgery will be analysed in the intention-to-treat population. Comparison between treatment arms will be done by means of Fisher’s exact test.

The absolute and relative incidence of toxicities related to the administration of induction chemotherapy or chemoradiotherapy will be presented by treatment arm, and analysed in all patients who received at least one dose of neoadjuvant chemotherapy (experimental arm) or chemoradiotherapy (control arm). Comparison between treatment arms will be done by means of Fisher’s exact test.

Comparison of health-related quality of life between the two treatment arms at baseline and over time will be performed by means of a random-effects regression model and will be based on the intention-to-treat group.

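### Fisher's exact test is the only comparison named for the surgical and histopathological outcomes; applied to the ordered Mandard grade it is valid but inefficient

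*Protocol article*

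**What the plan says.** The relevant paragraph of Statistical methods has three parts:

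- It opens with "Data on surgical characteristics, histopathological characteristics, and major surgical morbidity will be presented by treatment arm" and restricts these data to patients who had surgery.
- It then turns to a binary item: "The number of patients undergoing surgery will be analysed in the intention-to-treat population".
- It closes with "Comparison between treatment arms will be done by means of Fisher’s exact test". The sentence has no qualifier, and the paragraph names no other test.

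The Outcomes section shows what these headings contain. One secondary outcome is "pathological response, graded according to the Mandard grading system". The examples of surgical characteristics include "use of intraoperative radiotherapy, blood loss, duration of operation, intraoperative complications", so binary and continuous items sit side by side.

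For description, Statistical methods does separate data types: "Continuous data will be reported as mean (standard deviation) or median (interquartile range or 95 per cent confidence interval), depending on the distribution", with counts and percentages for categorical data. The comparison rule does not carry that distinction through.

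**The concern.** Mandard grade is an ordered scale. Fisher's test extended to a table with more than two columns treats the grades as unordered labels, so a consistent shift towards better response earns no more credit than a scattered difference of the same size. The result is a loss of power, not a false-positive problem.

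This matters because the Introduction gives greater local downstaging as the way induction chemotherapy might raise the R0 rate. Pathological response is a listed secondary outcome that bears directly on that mechanism. A real shift could be missed by a test that ignores the order.

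The same sentence also does not fit blood loss or operating time, because Fisher's test cannot be applied to a continuous measurement that has not been categorised.

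**Working it through.** **1. The plan's own figure.** The protocol states no power for pathological response. Its only sample-size figure is for R0: 45% vs 60%, two-sided 5%, 80% power.

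n per arm = [1.960·√(2 × 0.525 × 0.475) + 0.842·√(0.45 × 0.55 + 0.60 × 0.40)]² / 0.15²
= (1.384 + 0.588)² / 0.0225 = 172.8, so 173.

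This reproduces the stated 173 per arm (power at 173 is 80.05%). The present point does not touch it.

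**2. Number with a graded specimen.** The Sample size section expects 25% not to reach surgery. Applied to both arms, 0.75 × 173 = 129.75, so about 130 per arm.

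**3. Assumptions not in the documents.** Five grades; two control distributions, one peaked (10/15/30/30/15%) and one flat (20% each); and a proportional-odds shift towards better response. The experimental distribution comes from multiplying each cumulative odds by the odds ratio (OR). For example, for the peaked distribution at OR 1.8:

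- cumulative 0.10, 0.25, 0.55, 0.85 have odds 0.111, 0.333, 1.222, 5.667
- × 1.8 gives 0.20, 0.60, 2.20, 10.20, hence cumulative 0.167, 0.375, 0.688, 0.911
- grades: 16.7/20.8/31.3/22.3/8.9%.

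**4. Simulation.** 2,000 trials per scenario, 130 per arm, two-sided 5%. The unordered test is the Fisher-Freeman-Halton test on the 2 × 5 table (Monte Carlo p-value); the rank test is the Wilcoxon with tie correction.

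| OR | Control distribution | Unordered Fisher | Wilcoxon | Gap (points) |
|---|---|---|---|---|
| 1.0 | peaked | 5.4% | 5.2% | n/a |
| 1.0 | flat | 5.1% | 5.3% | n/a |
| 1.5 | peaked | 28.5% | 46.0% | 17.5 |
| 1.5 | flat | 25.4% | 44.1% | 18.8 |
| 1.8 | peaked | 54.1% | 75.2% | 21.1 |
| 1.8 | flat | 54.5% | 78.1% | 23.6 |
| 2.0 | peaked | 69.5% | 87.1% | 17.6 |
| 2.0 | flat | 68.6% | 87.2% | 18.6 |

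Monte Carlo standard error is at most √(0.5 × 0.5 / 2000) = 1.1 points. A second, separate simulation with 130 per arm and two assumed five-grade distributions gave about 27% vs 44%, 53% vs 76%, and 68-70% vs 88-89% at the three odds ratios. The ranges in the conclusion span both sets of runs.

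**5. Scope of the Fisher sentence.** The toxicity paragraph ends with the same sentence, and there it covers the whole paragraph. If in the surgical paragraph it covered only the number undergoing surgery, major surgical morbidity, a named secondary outcome, would have no comparison method. Both facts favour the paragraph-wide reading.

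**The case against.** The strongest reply is that the text is ambiguous. Surgical and histopathological data are only to be presented; the one item to be analysed is the number undergoing surgery, and the Fisher sentence follows it directly. In the toxicity paragraph the data are both presented and analysed, so the parallel is not conclusive. This stands as a caution: the paragraph-wide reading is the more natural one, but it is not certain, and the protocol does not say that Fisher's test is to be used for every item. Mandard grade is not named in the paragraph either; it falls under histopathological characteristics only by inference.

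It is also fair to say that Fisher's test on an ordered table is valid and holds its size, and that pathological complete response, which the Introduction discusses, is binary and suits Fisher's test well. Both are accepted. The criticism is of efficiency on the full scale.

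A reader might infer that the rule forces blood loss and operating time to be dichotomised after the fact. The documents do not support that. They give no cut-points, and continuous data may simply be described by means or medians. That no test is named for these items is a detail normally left to the analysis plan.

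A reader might also extend the point to radiological response (mrTRG). That outcome lies outside this paragraph and no test is named for it, so it is not part of the finding. Nor do the documents call Mandard grade the main measure of downstaging; it is one secondary outcome among many.

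**Conclusion.** The point holds as a modest one about secondary outcomes. The protocol names a single unqualified test for a paragraph that, on its more natural reading, includes an ordered response grade. On that reading, and if the full scale is tested, the unordered test gives up about 17 to 24 percentage points of power in the tabulated runs: about 25-28% vs 43-46% at OR 1.5, 53-55% vs 75-78% at OR 1.8, and 68-70% vs 87-89% at OR 2.0 across both sets of runs.

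These figures rest on 130 operated patients per arm, five grades, the assumed control distributions and a proportional-odds shift. Only the first derives from the protocol. The direction is the same under both tabulated control distributions. The Fisher analysis would not be invalid, and the primary R0 analysis, the sample size and the type I error are unaffected.

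**What to change.** Reword the closing sentence of the paragraph so that Fisher's exact test applies to binary and unordered categorical items, such as the number undergoing surgery, major surgical morbidity and pathological complete response. Add that Mandard grade is compared between arms by a Wilcoxon rank-sum test or a proportional-odds model. State that blood loss and duration of operation do not fall under the Fisher sentence: they are either described only or, if compared, analysed by a rank-sum test or a linear model on a suitable scale.

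The cost is a few lines of wording in the protocol or analysis plan, with no new data and no change to the sample size. It should be settled before any comparison by arm is seen, so that neither the test nor a grouping of grades is chosen with the results in view.

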### Potential benefits and disadvantages of induction chemotherapy

Induction chemotherapy in addition to neoadjuvant chemo(re)irradiation has the potential to induce more local tumour downstaging than can be achieved with chemoradiotherapy alone owing to the supplementary effect of the induction chemotherapy, and possibly also the synergistic effect of induction chemotherapy and chemoradiotherapy^18^. Improved local downstaging may subsequently increase the R0 resection rate, which has been identified as the main prognostic factor for overall survival^6–8^. When local downstaging is excellent, a pathologic complete response (pCR) can be achieved, which is a predictive variable for survival in patients with LRRC^19^. With improved local downstaging, the proportion of patients with a pCR may also increase. Alongside the local effect, induction chemotherapy may also have the potential to eradicate micrometastases^20^.

The addition of induction chemotherapy also has potential drawbacks. First, induction chemotherapy is associated with toxicity^21^. Second, chemotherapy-induced morbidity could delay, reduce or prevent subsequent treatment with chemoradiotherapy and surgery. Third, when chemoradiotherapy is preceded by induction chemotherapy, the toxicity of chemoradiotherapy may be increased. Finally, the prolonged and intensified neoadjuvant course may influence the patient’s performance status and may have a negative effect on surgical morbidity and mortality rates. Furthermore, prolonged neoadjuvant treatment may increase the risk of disease progression and secondary unresectability.

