#### Induction chemotherapy

Patients allocated to the experimental arm will start treatment with induction chemotherapy within 4 weeks after randomization. Induction chemotherapy will consist of either three 3-week cycles of CAPOX (oxaliplatin 130 mg per m^2^ body-surface area (BSA) intravenously (i.v.) on day 1, capecitabine 1000 mg per m^2^ BSA, orally, twice daily on days 1–14), four 2-week cycles of FOLFOX (85 mg per m^2^ BSA of oxaliplatin i.v. on day 1, 400 mg per m^2^ BSA of leucovorin i.v. on day 1, 400 mg per m^2^ BSA of bolus 5-fluorouracil i.v. on day 1 followed by 2400 mg per m^2^ BSA of continuous 5-fluorouracil i.v. on days 1–2), or four 2-week cycles of FOLFIRI (180 mg per m^2^ BSA of irinotecan i.v. on day 1, 400 mg per m^2^ BSA of leucovorin i.v. on day 1, 400 mg per m^2^ BSA of bolus 5-fluorouracil i.v. on day 1 followed by 2400 mg per m^2^ BSA of continuous 5-fluorouracil i.v. on days 1–2). The choice of chemotherapy agent will be left to the physician’s discretion.

After three cycles of CAPOX or four cycles of FOLFOX or FOLFIRI, pelvic MRI will be performed for local restaging, and high-dose thoracoabdominal CT for restaging of possible distant metastases. Restaging imaging will be discussed during a dedicated MDT meeting in one of the expert centres. If a patient develops distant metastases or local disease becomes unresectable, best palliative treatment will be offered according to the standard of care. If a patient has progressive local disease, but surgery is still considered feasible, no further systemic therapy will be administered and patients will start treatment with chemoradiotherapy. If a patient has stable or responsive disease, induction chemotherapy will be continued with either one 3-week cycle of CAPOX or two 2-week cycles of FOLFOX or FOLFIRI.

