#### Restaging

Four to 6 weeks after the last day of radiotherapy, pelvic MRI will be performed for local restaging and high-dose thoracoabdominal CT for restaging of possible distant metastases. Restaging imaging will be discussed during a dedicated MDT meeting in one of the expert centres. In the event of distant metastases or unresectable local disease, best palliative treatment will be offered. Patients with resectable disease will undergo surgery.

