### Sample size

Currently, an R0 resection is achieved in approximately 60 per cent of patients undergoing surgery after treatment with neoadjuvant chemoradiotherapy^16^^,^^17^. However, 25 per cent of patients who start neoadjuvant chemotherapy are not eligible for surgery owing to progressive disease: local progression, distant progression, or death from progression^12^. This means that an R0 resection is obtained in only 45 per cent of patients (75 per cent of 60 per cent) who start with intentionally curative treatment. The study hypothesis is that there will be a 15 per cent increase in the R0 resection rate (from 45 to 60 per cent) for patients in the experimental arm. A χ^2^ test with a 5 per cent two-sided significance level indicated that the study would have 80 per cent power to detect a significant difference of 15 per cent between the two groups (given that the percentage in the control group is 45 per cent) when the sample size in each group is 173 patients. With an expected dropout of 5 per cent, the total requirement was calculated as 364 patients.

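### Pathological response is derived only in operated patients and, on the natural reading, tested between arms there, so that comparison is not randomized and could be distorted in either direction

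*Protocol article*

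**What the plan says.** The Outcomes section lists as a secondary outcome "pathological response, graded according to the Mandard grading system". The Statistical methods section groups surgical characteristics, histopathological characteristics and major surgical morbidity, and states that these "will be presented by treatment arm, and will be derived only for patients who underwent surgery". The next sentence places the number of patients undergoing surgery in the intention-to-treat population. The paragraph then closes with "Comparison between treatment arms will be done by means of Fisher’s exact test". No other analysis set or test is given for pathological response. The primary endpoint, R0 resection, is analysed by intention to treat.

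Patients can leave the path to surgery at two points. After induction chemotherapy, in the experimental arm only: "If a patient develops distant metastases or local disease becomes unresectable, best palliative treatment will be offered according to the standard of care". At restaging after chemoradiotherapy, in both arms: "In the event of distant metastases or unresectable local disease, best palliative treatment will be offered". The Sample size section expects that "25 per cent of patients who start neoadjuvant chemotherapy are not eligible for surgery owing to progressive disease".

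The Introduction gives reasons why induction could move the operated share either way. It may improve downstaging ("With improved local downstaging, the proportion of patients with a pCR may also increase"), but "prolonged neoadjuvant treatment may increase the risk of disease progression and secondary unresectability".

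**The concern.** Mandard grade is read on the resection specimen, so a table for operated patients is natural as description. A between-arm test in that group is a different matter. Membership of the group is decided after randomization by events that the experimental treatment can influence. If the arms lose different shares of patients, or lose them for different reasons, the operated groups are no longer comparable. The pCR proportions can then differ without any effect on response, or a real effect can be hidden.

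The Introduction presents pCR as a possible benefit and as a predictor of survival. It also notes that two retrospective series in locally recurrent disease had promising pCR rates while their R0 rates did not appear improved. If R0 turns out neutral, a P value for pathological response could carry weight in the trial's message. That P value should come from a randomized comparison.

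**Working it through.** **The plan's own figure.** The Sample size section takes 60% R0 among operated patients and 75% reaching surgery: 0.75 × 0.60 = 0.45. The 45% control rate therefore counts unoperated patients as not having R0. From 45% vs 60%, two-sided 5% level and 80% power, the stated 173 per group reproduces (power 0.800). The article gives no planning figure for pathological response, so what follows is an illustration.

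**Inputs**
- 182 per arm: 364 / 2 (Sample size).
- 75% of controls operated: Sample size.
- pCR 17% among operated controls: the figure reported for two retrospective series (Current evidence). Those series were induction-treated and the article does not state the denominator, so its use as an operated-control rate is an assumption.
- Share operated in the experimental arm: assumption, varied from 60% to 85%.
- Broader good response in 30% of randomized patients: assumption.
- No treatment effect: the same proportion of randomized patients achieves the response in both arms, and unoperated patients have not achieved it.

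**Formula.** Rate among operated = rate per randomized patient / share operated. For pCR the rate per randomized patient is 0.75 × 0.17 = 0.1275. The chance that a two-sided Fisher test gives P < 0.05 was obtained by exact enumeration, with 136 operated controls.

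**pCR, 12.75% of randomized patients in both arms**

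| Experimental arm operated | Operated patients, control vs experimental | Operated-only pCR, control vs experimental | Fisher rejection |
|---|---|---|---|
| 70% | 136 vs 127 | 17.0% vs 0.1275/0.70 = 18.2% | 4.9% |
| 65% | 136 vs 118 | 17.0% vs 0.1275/0.65 = 19.6% | 7.3% |
| 60% | 136 vs 109 | 17.0% vs 0.1275/0.60 = 21.3% | 11.6% |
| 85% | 136 vs 155 | 17.0% vs 0.1275/0.85 = 15.0% | 6.5% |

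With all 182 vs 182 randomized patients as the denominator, rejection is 3.4%.

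**Broader response, 30% of randomized patients in both arms** (0.30/0.75 = 40.0% of operated controls)
- 65% operated: 0.30/0.65 = 46.2%, rejection 15.0%.
- 60% operated: 0.30/0.60 = 50.0%, rejection 31.3%.
- All randomized: rejection 3.8%.

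**The opposite assumption.** Suppose instead that losses are unrelated to local response and that the rate among operated patients is truly equal. With 60% of the experimental arm operated, the all-randomized comparison gives 0.75 × 17% = 12.75% vs 0.60 × 17% = 10.2% (rejection 8.7%). For a 40% response among operated patients it gives 30% vs 24% (rejection 22%). The all-randomized measure therefore responds to operability as well as to response.

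**The case against.** **The test may not apply to pathology.** The Fisher sentence directly follows the one on the number undergoing surgery and may refer only to that. The list before it includes surgical characteristics such as blood loss and operating time, for which Fisher's test does not fit as continuous measures, so the sentence cannot literally cover every item. The paragraph also says histopathological characteristics, not pathological response. This stands as an ambiguity. Still, the sentence closes the paragraph, and pathological response is given no other set or test, so a tested operated-only comparison remains the natural reading. If only description was meant, the wording should say so.

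**The worst responders do not simply vanish.** A reader might infer that patients who miss surgery are all local non-responders and that the comparison is bound to flatter induction. The documents do not support this. The reasons listed for missing surgery include distant progression and death. Patients with local progression after induction whose surgery is still feasible continue to chemoradiotherapy. The extra restaging may only find earlier what the later one would have found. The direction is open.

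**The size rests on assumed shares.** This also stands. None of the experimental operated shares comes from the article, and a 5-point difference leaves the pCR rejection rate below 5%. A larger difference would show in the number operated, which is reported by intention to treat.

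**The alternative is not neutral.** Counting unresected patients as not achieving pCR mixes operability with response, as the last calculation shows. It does keep the randomized groups intact and matches how R0 is handled. It answers a composite question and must be labelled as such.

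**Conclusion.** The point holds in a limited form. On the natural reading, pathological response is tested between arms in a group defined after randomization, and the article itself gives reasons why induction could change who enters that group. There is no distortion if the arms lose equal shares of similar patients. For pCR, under the stated assumptions, the distortion is negligible at a 5-point difference in operability and modest at 10 to 15 points (2.6 to 4.3 percentage points, rejection 7% to 12%). For the assumed broader category it is larger (rejection 15% to 31%). Where some unoperated patients did respond locally, it would be smaller than shown. The outcome is secondary and the intention-to-treat analysis of R0 is not affected. It is worth correcting because the correction is cheap.

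**What to change.** In the Statistical methods section, make the tested between-arm comparison the proportion with pCR (or a prespecified good response) among all randomized patients, with patients without a resection counted as not having achieved it, in line with R0. Label it a composite of reaching surgery and response. Keep the Mandard distribution in operated patients as description by arm, without a between-arm P value and next to the number operated. State which outcomes the Fisher sentence covers.

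The cost is wording only, with no new data. The downsides are that the pCR percentage will be lower than in operated-only series and that the measure mixes operability with response. The descriptive table keeps comparability with those series.

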#### Chemoradiotherapy

Patients in the experimental arm will start chemoradiotherapy within 3–5 weeks after the first day of the last cycle of chemotherapy. Patients in the control arm will start chemoradiotherapy within 4 weeks after randomization. The radiotherapy dose will depend on whether the patient received radiotherapy previously. In radiotherapy-naive patients, full-course radiotherapy will consist of 25 × 2.0 Gy or 28 × 1.8 Gy radiotherapy. In patients with a history of radiotherapy, the radiotherapy dose will consist of 15 × 2.0 Gy. The target volume will be defined by the gross, clinical, and planning target volumes (GTV, CTV and PTV respectively), and will be similar for radiotherapy-naive and previously irradiated patients. The GTV contains all macroscopic visible tumour, the CTV includes the GTV with a margin of 1 cm, without adjustment of the CTV towards other organs, and the PTV includes the CTV with a margin that can be determined according to local policy. Concomitant chemotherapy will comprise capecitabine, administered orally at a dose of 825 mg/m^2^ twice daily on radiotherapy days. In the event of unacceptable toxicity caused by capecitabine during induction chemotherapy, concomitant tegafur/gimeracil/oteracil administered orally at a dose of 25 mg/m^2^ twice daily on radiotherapy days may be prescribed at the physician’s discretion.

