#### Surgery

Surgery will be performed by experienced surgical oncologists within 10–14 weeks after completion of chemoradiotherapy. The type of surgery will depend on the location of the recurrence and involvement of adjacent structures, and will be left to the discretion of the surgeon. When deemed necessary and feasible by the surgeon and radiation oncologist, intraoperative radiotherapy may be administered by either intraoperative electron beam radiotherapy or high-dose-rate intraoperative brachytherapy^38^^,^^39^.

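### For chemoradiotherapy toxicity, the stated analysis set dilutes the experimental-arm rate but not the control rate; the set suits only total neoadjuvant toxicity

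*Protocol article*

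**What the plan says.** The Outcomes section of the protocol article lists two toxicity outcomes, each with its own window. Induction toxicity is "scored from day 1 of the first cycle of induction chemotherapy until 1 month after the final administration". Chemoradiotherapy toxicity is "scored from start of radiotherapy until 3 months after the final dose of radiotherapy".

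Statistical methods then treats both in one sentence. It begins "The absolute and relative incidence of toxicities related to the administration of induction chemotherapy or chemoradiotherapy will be presented by treatment arm" and goes on to say that they will be "analysed in all patients who received at least one dose of neoadjuvant chemotherapy (experimental arm) or chemoradiotherapy (control arm". The test follows: "Comparison between treatment arms will be done by means of Fisher’s exact test". The general rule is "All statistical tests will be two-sided and *P* < 0.050 will be classified as statistically significant".

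Three other parts of the article bear on this:

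- **Induction chemotherapy.** Experimental patients found at mid-induction restaging to have metastases or unresectable disease go to palliative treatment, so they never start chemoradiotherapy.
- **Chemoradiotherapy.** Experimental patients are to "start chemoradiotherapy within 3–5 weeks after the first day of the last cycle of chemotherapy".
- **Introduction (potential benefits and disadvantages).** Two of the listed drawbacks are that induction may make the later chemoradiotherapy more toxic, and that its morbidity may keep patients from receiving chemoradiotherapy at all.

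**The concern.** A control patient enters the toxicity set only by starting chemoradiotherapy. An experimental patient enters by starting chemotherapy and stays in the denominator even if chemoradiotherapy is never given. Such a patient cannot have chemoradiotherapy toxicity and counts as event-free for that outcome. The experimental rate is therefore pulled down for a reason unrelated to how chemoradiotherapy is tolerated.

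The direction matters. The pull favours the experimental arm on a harm the authors list as a possible cost of their strategy. A real increase could be missed, or equal tolerance could look like an advantage.

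A smaller, related issue is that the induction window can still be open when the chemoradiotherapy window begins. An event in that interval is eligible for either outcome. Relatedness may not separate the two, because capecitabine is both part of CAPOX and the concomitant agent.

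**Working it through.** **Plan's own figure.** The article gives no figure for the toxicity comparison. Its sample size supplies the number per arm used below, and it reproduces. For 45% vs 60%, two-sided 5%, 80% power and mean proportion 0.525:

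n = [1.960 × √(2 × 0.525 × 0.475) + 0.842 × √(0.45 × 0.55 + 0.60 × 0.40)]² / 0.15² = (1.384 + 0.588)² / 0.0225 ≈ 172.8, so 173 per arm.

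**Inputs for the dilution.** Let p be the chemoradiotherapy toxicity rate among those who start it, and q the share of the experimental set that never starts it. Neither is in the article, so both are assumed. The one related figure is in Sample size: 25% not eligible for surgery because of progression. That is loss before surgery, not before chemoradiotherapy, and serves here only as an extreme.

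**Formula.** Experimental rate on the stated set = p × (1 − q). Control rate = p.

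**Case 1: same true rate of 30% in both arms.** The last column is the exact probability, with 173 per arm, that Fisher's test is significant in favour of the experimental arm.

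| q | Experimental rate on stated set | Falsely favours experimental |
|---|---|---|
| 0 | 30.0% | 1.9% |
| 5% | 0.30 × 0.95 = 28.5% | 3.9% |
| 10% | 0.30 × 0.90 = 27.0% | 7.2% |
| 15% | 0.30 × 0.85 = 25.5% | 12.6% |
| 25% (extreme) | 0.30 × 0.75 = 22.5% | 31.0% |

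**Case 2: a true excess among starters, 40% experimental vs 30% control.** Power is the probability of a significant Fisher result. With starters only, the experimental arm has 156, 147 or 130 patients (173 × (1 − q), rounded) against 173 controls.

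| q | Experimental rate on stated set | Power, stated set | Power, starters in both arms |
|---|---|---|---|
| 0 | 40.0% | 45.2% | 45.2% |
| 10% | 0.40 × 0.90 = 36.0% | 18.8% | 45.4% |
| 15% | 0.40 × 0.85 = 34.0% | 10.3% | 44.7% |
| 25% (extreme) | 0.40 × 0.75 = 30.0% | 3.8% | 42.1% |

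At q = 25% the ten-point excess cancels exactly.

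**Window overlap.** Count from day 1 of the last cycle and take one month as 30 days. Chemoradiotherapy at 3, 4 or 5 weeks starts on day 22, 29 or 36.

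- CAPOX: last capecitabine on day 14, so the induction window ends on day 14 + 30 = 44. The overlap, counting both end days, is 23, 16 or 9 days. It occurs at every permitted start.
- FOLFOX or FOLFIRI: last infusion on day 2, so the window ends on day 32. The overlap is 11, 4 or 0 days.

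Taking a month as 28 or 31 days gives 7–21 or 10–24 days for CAPOX, and 0–9 or 0–12 days for the other two. No number of doubly counted events can be derived, because the article states no counting rule.

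**The case against.** **The set is conventional.** Read as one comparison of all neoadjuvant toxicity, the sentence includes everyone who started the first treatment of their arm, like for like. That stands, and the set should be kept for that purpose. It does not answer the point for chemoradiotherapy toxicity, which Outcomes lists separately and Statistical methods assigns to the same set.

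**Safety denominators belong in an analysis plan.** Often they do, and a rule for overlapping windows is the kind of detail usually found there. But the analysis set and the test are stated here, so the denominator is a fixed choice and not missing detail.

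**Other data would reveal the harm.** Serious adverse events are recorded from randomization, the safety board tabulates patients who cannot complete chemoradiotherapy, and compliance is an outcome. These help, so the harm would not be invisible. None of them is a comparison of graded chemoradiotherapy toxicity.

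**The size is assumed and modest.** Correct. A shift of 1.5 to 4.5 points is less than one standard error of the difference, √(2 × 0.30 × 0.70 / 173) = 4.9 points. But the shift is systematic, and in Case 2 it removes 4 to 6 of the 10 points to be detected (q of 10–15%).

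**Restricting to starters has its own bias.** This stands. Starting chemoradiotherapy is a post-randomization event, and if induction morbidity removes the frailest experimental patients, the remaining comparison may also favour that arm. The starters analysis can only be a supplement.

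Three stronger readings may tempt a reader, and the article does not support them:

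- *Events are counted twice.* Toxicities are selected by their relation to a treatment, not by date alone, and a per-patient incidence of any toxicity counts a patient once. Overlapping windows make double counting possible; nothing prescribes it.
- *Surgical complications are scored as chemoradiotherapy toxicity.* Surgery comes "within 10–14 weeks after completion of chemoradiotherapy", so it can fall inside the three-month window. But surgical morbidity has its own outcome and its own scale (Clavien–Dindo), relatedness screens such events, and the timing is the same in both arms.
- *An experimental patient who goes straight to chemoradiotherapy is in no set.* This depends on reading neoadjuvant chemotherapy as induction only. If it includes the concomitant capecitabine, the patient is in. The dilution is present under either reading.

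**Conclusion.** The point holds for one outcome. On the stated set, the experimental chemoradiotherapy toxicity rate is (1 − q) times the rate among those treated, while the control rate is undiluted, so the comparison is tilted against finding a harm the article itself names. With assumed q of 5–15% and a true 30% in both arms, the experimental arm reads 28.5% to 25.5%. With a true 40% vs 30% among starters, power falls from about 45% to 19% (q = 10%) or 10% (q = 15%). These figures rest on assumed values of q and of the toxicity rates, and on 173 patients in each set; only the direction and the factor (1 − q) follow from the text.

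The overlap of the induction and chemoradiotherapy windows is certain after CAPOX and depends on timing after FOLFOX or FOLFIRI. It is an ambiguity to settle, not a demonstrated counting error. Nor is the stated set wrong as such. This is a secondary safety outcome: the R0 analysis and the sample size of 364 are untouched.

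**What to change.** 1. Keep the stated set for total neoadjuvant toxicity by arm, defined as all patients who started any allocated neoadjuvant treatment. This wording also settles the case of an experimental patient who goes straight to chemoradiotherapy.
2. Add chemoradiotherapy toxicity among patients who started chemoradiotherapy, in both arms. Label it as a post-randomization subset, show it beside the total-toxicity comparison, and report how many in each arm did not start.
3. Describe induction toxicity in the experimental arm only, without a test between arms.
4. State one attribution rule for events in the overlap of the two windows, for example by judged relatedness with a stated default when both treatments are plausible. Count each patient once in the total.

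The cost is wording, derivation rules and one extra table; no new data are needed. The downside is that the added comparison conditions on starting chemoradiotherapy, so it supplements the stated set and does not replace it. In an open-label trial the choice should be fixed before the toxicity data are compared by arm, so that the denominator is not chosen afterwards.
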